Diet plays a crucial role in the development and composition of the gut microbiota. Various dietary factors influence the gut microbiota. Among others, the quantity and balance of macronutrients (carbohydrates, protein, and fat) have attracted a particular attention [22]. Dong et al. found that a calorie-restricted high protein diet had beneficial effects on microbial diversity and alteration in *Akkermansia spp*. and *Bifidobacterium spp*., as well as the loss of *Prevotella spp*., when compared to baseline [23]. On the other hand, a high-carbohydrate diet has been linked to dysbiosis and an increase in anaerobic pathogen species, most notably *Bacteroides* [24]. No specific diet has been recommended to manage patients with MetS so far. Several studies have demonstrated that the Mediterranean and DASH diets are effective at reducing insulin resistance and other components of metabolic syndrome [25, 26]. However, none of these diets have focused on the dietary macronutrient composition. Despite the worldwide recommendation on reduced fat intake, the prevalence of this syndrome has increased [27]. Therefore, it seems that the advice on low fat diets, in spite of their beneficial effects on some components of this syndrome, might not be an appropriate choice for managing metabolic syndrome [28]. High-protein diets have also been linked to kidney dysfunction, acidosis, and insulin resistance [29]. However, dietary carbohydrate restriction might be a suitable choice because earlier studies have shown that consumption of this dietary pattern has been resulted in improved components of MetS, even in the absence of weight loss [30]. Furthermore, low-carbohydrate diets outperform low-fat diets in terms of weight loss and adipose tissue reduction [31, 32]. This is particularly relevant in Middle Eastern countries, where people get more than 60% of energy from carbohydrates, in particular from refined sources [33]. High carbohydrate intake has also been blamed as one of the primary causes of the high prevalence of metabolic syndrome in Iranians [34]. In this regard, Rajaie et al. conducted a randomized crossover clinical trial in which they applied a carbohydrate-restricted diet by substituting dietary fats; this regimen contained 43–47% carbohydrate and 36–40% dietary fat. After 3 months of follow-up, a moderate-restricted carbohydrate diet reduced blood pressure, waist and hip circumferences, and the prevalence of the metabolic syndrome [35]. To the best of our knowledge, no earlier study has examined the effect of such dietary pattern on the gut microbiome composition in patients with metabolic syndrome. Understanding the diversity and composition of gut microbiome will aid researchers in developing novel MetS prevention and treatment strategies. As a result, the aim of this study is to (i) determine the effect of a moderately restricted carbohydrate diet on gut microbiota composition and metabolic parameters in women with metabolic syndrome and (ii) determine whether these potential changes in the gut microbiota will be sustained during a subsequent six-month weight maintenance phase.

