### Intervention

Participants will be randomly assigned into one of the two above-mentioned groups. During an hour-long discussion, each participant will be instructed on either the MRC diet or NWL diet. All participants will receive a calorie restricted diet based on their status of weight and BMI (300–500 kcal less than participant’s energy requirement). We will compute calorie requirements based on resting energy expenditure (using the Harris-Benedict equation) and physical activity levels. The main distinction between these two diets will be the proportion of calories derived from fats and carbohydrates. The MRC diet will be defined as 42–45% of energy from carbohydrates and 35–40% from fats, while the NWL diet will be defined as 52–55% of total calories from carbohydrates and 25–30% from fats. In fact, 10% of energy from carbohydrates in the MRC diet will be substituted with non-hydrogenated vegetable oils. Dietary protein intakes will be accounted for 15–17% of total energy across both dietary groups. The first phase of the study in which subjects will receive the aforementioned diets will last for 3 months. Then participants will enter the second phase, in which all participants will be followed for another 6 months on a weight-maintenance (WM) diet containing a normal proportion of macronutrients, including 52–55% carbohydrates, 27–30% fat, and 15–17% protein. The main objective of this phase is to determine whether the changes caused by the intervention will be maintained after six months. In addition, it will be determined if changes in gut microbiota persist after 6 months of a weight-maintenance diet and to what extent these changes might contribute to weight maintenance and the stabilization of metabolic variables after 6 months.

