### Biochemical assessments

A blood sample will be taken from each patient’s venous blood at the study baseline, end of the first phase (after 3 months), and end of the second phase of the study (after 9 months) following 12 h of fasting. We will use a portion of the blood sample to evaluate glucose levels and lipid profile. The remaining serum will be kept at – 80 °C until it is further analyzed for insulin levels. Plasma glucose and lipid profile concentrations (TC, HDL, LDL, and TG) will be determined via an enzymatic colorimetric method using commercial kits. Finally, the serum insulin concentrations will be examined using electrochemiluminescence (ECL) method. We also will determine insulin resistance (HOMA-IR) and quantitative insulin-sensitivity check index (QUICKI) formulas.

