### Stool samples and gut microbiota assessment

A 10-g stool sample will be collected from each participant at study baseline, 3 months after intervention, and 6 months after the end of intervention using a stool specimen collection kit that will be brought to the clinic in ice packs within 4 h. Until fecal microbial analysis, stool samples will be frozen at – 80 °C in the laboratory. To minimize changes in the quantity of fecal bacteria, we will collect stool samples in one of three ways: first, we will invite patients to visit the laboratory on the day of fecal sampling. The lab will be equipped with all of the necessary equipment to collect fecal samples. The second method requires the patient to transport the sample to the laboratory within 4 h of their sampling. Finally, if the patient is unable to complete any of the prior approaches, they should contact the study researchers, who will collect their sample at their home and transfer it within 4 h to the lab.

DNA extraction from 200 mg of frozen stool samples will be done using a FavorPrep Stool DNA Isolation Mini Kit (Favorgen Biotech Corp., Taiwan) according to the manufacturer’s instructions. The extracted bacterial DNA purity and concentration will be determined by Nanodrop spectrophotometer (Thermo Scientific NanoDrop, USA). All the extracted DNAs will be stored at − 20 °C freezer until further analysis. Additionally, the quantity of fecal bacteria, including Firmicutes, Bacteroidetes, *Bifidobacteria*, *Lactobacillus*, *Clostridium*, *Prevotella*, *Bacteroidetes*, and *Akkermansia muciniphila*, will be determined using a quantitative real-time polymerase chain reaction (qRT-PCR) in duplicate. We selected the taxa based on their association with metabolic syndrome and their ability to balance the gut microbiota [39, 40]. Specific primers targeting the bacterial 16S rRNA genes blasted in NCBI will be used in the current study. Each reaction mixture is composed of SYBR Premix Ex Taq II (Takara, China), the specific forward and reverse primers, and a DNA template. The thermal cycling conditions will be as follows: an initial DNA denaturation step at 95 °C for 1 min, 40 cycles of denaturation at 95 °C for 5 s, primer annealing at 55 °C for 30 s, and extension at 72 °C for 30 s. Finally, in order to confirm the specificity of the amplification products, melting curve analysis will be performed by slowly cooling the PCRs from 95 °C to 60 °C.

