### Statistical analysis

All statistical analyses will be carried out using the SPSS software version 25 (SPSS Inc., Chicago, IL, USA). For addressing non-adherence, the intention-to-treat (ITT) analysis will be applied [41]. Moreover, we will apply the last observation carried forward method (LOCF) to handle missing values [42]. In order to determine the normal distribution of variables, we will use the Kolmogorov-Smirnov test, histogram, and Q-Q plot. We will log transform (ln) the data, if necessary, to achieve normal distribution. Data will be presented as mean ± standard deviation (SD) for continuous variables and as percentages for categorical variables. Chi-square test and independent samples *t*-test will be used for comparing continuous and categorical variables between the two groups, respectively. We also will use the paired-sample *t* test for within-group comparisons. Repeated measures analysis of variance will be employed to determine the impact of the intervention on the outcome variables. These analyses will examine the effects of the intervention, time, and the interaction between time and intervention. Any potential differences in baseline levels of outcome variables, dietary intakes, and physical activity will be controlled in these analyses. Statistical significance will be defined as *P* values less than 0.05.

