## Strengths and limitations

This is the first clinical trial examining the effect of a moderately restricted carbohydrate diet on the composition of gut microbiota and several metabolic parameters in patients with MetS. It should be noted that the intervention is low-cost and no extra charge would be imposed to patients. Stratified block randomization will be used to match patients based on a number of confounding variables that may influence the outcomes. Additionally, participants will be recruited through public announcements. Thus, all volunteers may be encouraged to adhere to dietary recommendations. Another potential strength of the study is the measurement of gut microbiota composition and biochemical parameters not only during the intervention but also after the intervention, during the maintenance phase. Dietary intakes and physical activity will be evaluated during both phases of the study as well.

There are several limitations to this study that should be considered. The major limitation of the current trial is the small number of bacterial species and biochemical parameters that will be examined. Moreover, we are concerned about gut microbiota changes during sample collection. In order to prevent this, stool samples will be collected in the laboratory and immediately frozen at − 80 °C. In addition, we strive to have all stool samples delivered to the laboratory within 4 h of collection. Nevertheless, several samples may arrive within more than four hours. Even though biomarkers could provide more accurate measures for validating dietary records, we will not use them to evaluate diet compliance due to financial constraints. This study will be conducted during the COVID-19 pandemic, which could increase the number of participants who are lost to follow-up.

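### Carrying the last observation forward sets every missing 9-month value to no change since month 3, which favours apparent maintenance if means move in phase II

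*Protocol article*

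**What the plan says.** All statements are in the protocol article.

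- **Missing data and analysis set (Statistical analysis).** "For addressing non-adherence, the intention-to-treat (ITT) analysis will be applied", and "we will apply the last observation carried forward method (LOCF) to handle missing values". LOCF is the only method named, and it is not restricted to an outcome or a phase. The named analyses are repeated measures ANOVA (intervention, time and their interaction) and paired t tests within groups.
- **Visits.** Under Biochemical assessments, blood is taken at baseline, "end of the first phase (after 3 months), and end of the second phase of the study (after 9 months". Under Stool samples and gut microbiota assessment, stool is collected "at study baseline, 3 months after intervention, and 6 months after the end of intervention". Read together, both schedules are months 0, 3 and 9.
- **Purpose of phase II.** The Intervention section states: "The main objective of this phase is to determine whether the changes caused by the intervention will be maintained after six months". The Background gives as aim (ii) to "determine whether these potential changes in the gut microbiota will be sustained during a subsequent six-month weight maintenance phase".
- **Diet change at month 3 (Intervention).** After the assigned diets end, "all participants will be followed for another 6 months on a weight-maintenance (WM) diet", which is the same for both arms.
- **Losses.** Sample size calculation assumes 10% dropout per arm and does not split it by phase. Strengths and limitations warns that the pandemic "could increase the number of participants who are lost to follow-up", without a figure.

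**The concern.** With three visits, only two values can be carried forward. A woman lost in phase II has her month-3 value entered at month 9. A woman lost in phase I has her baseline entered at months 3 and 9. In both cases her change from month 3 to month 9 is recorded as zero, and zero change is what maintenance means. The imputation therefore supplies an answer to the phase II question for each woman whose answer is unknown.

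The design makes this assumption hard to defend. The carried value was obtained at the end of the assigned diet, and both arms then move to a common diet. Month 3 is the point at which a shift in means is most plausible.

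At stake is the size of the change reported for phase II, within arms and between arms, for the metabolic outcomes and for the microbiota. Losses in phase I have a different effect: they dilute the 3-month difference, which works against the intervention.

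**Working it through.** **Inputs from the document (Sample size calculation).** Two-sided alpha 0.05, power 80%, SD 3.5, difference 2.5 for HDL-C (taken as mg/dL, the unit in the inclusion criteria), 10% dropout, 35 per arm.

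**Inputs assumed.** Phase II loss p of 10%, 20% or 30%, equal in both arms; correlation between visits of 0.3 to 0.7. The document gives neither.

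**Step 1. The plan's own figure.** n = 2 × (1.96 + 0.84)² × 3.5² / 2.5² = 30.8, rounded up to 31. Then 31 / 0.9 = 34.4, rounded up to 35 per arm. The stated sample size reproduces and is not affected by this point.

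**Step 2. Expected result under LOCF.** Let D3 and D9 be the true differences between arms at months 3 and 9. If dropout in phase II is random with share p,

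LOCF difference at month 9 = (1 − p) × D9 + p × D3.

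The bias is p × (D3 − D9), and the estimated 3-to-9-month change is (1 − p) times the true change. The same shrinkage applies within an arm and to any outcome on the scale analysed. If D9 = D3 the bias is zero.

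**Step 3. Numbers with D3 = 2.5.**

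| Phase II loss | LOCF difference at month 9, truth 0 | Share retained under LOCF, truth 50% |
|---|---|---|
| 10% | 0.10 × 2.5 = 0.25 | (0.9 × 1.25 + 0.25) / 2.5 = 55% |
| 20% | 0.20 × 2.5 = 0.50 | (0.8 × 1.25 + 0.50) / 2.5 = 60% |
| 30% | 0.30 × 2.5 = 0.75 | (0.7 × 1.25 + 0.75) / 2.5 = 65% |

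**Step 4. Rejection rate of a 9-month comparison between arms when the true 9-month difference is 0.** This was simulated with 35 per arm, SD 3.5 and a 2.5 difference at month 3, over correlations 0.3 to 0.7, with and without adjustment for baseline.

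| Phase II loss | Rejection rate (nominal 5%) |
|---|---|
| 10% | about 6–7% |
| 20% | about 8–12% |
| 30% | about 13–21% |

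The upper ends occur only at correlation 0.7 with baseline adjustment. An unadjusted comparison with exactly 4, 7 or 10 leavers per arm gives 6.2%, 8.4% and 12.1%. The last is slightly below the range because 10 of 35 is under 30%.

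**Step 5. Informative dropout (an assumption, for illustration).** Suppose that within an arm with a 2.5 gain, completers lose 1.0 and leavers lose all 2.5. True loss = (1 − p) × 1.0 + p × 2.5; LOCF loss = (1 − p) × 1.0.

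| Phase II loss | Truly retained | Retained under LOCF |
|---|---|---|
| 10% | 1 − 1.15/2.5 = 54% | 1 − 0.90/2.5 = 64% |
| 20% | 1 − 1.30/2.5 = 48% | 1 − 0.80/2.5 = 68% |
| 30% | 1 − 1.45/2.5 = 42% | 1 − 0.70/2.5 = 72% |

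Apparent maintenance rises with dropout while true maintenance falls.

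**Step 6. Losses in phase I.** If a share q is lost before month 3 and baseline is carried forward, the expected 3-month difference is (1 − q) × 2.5, for example 0.9 × 2.5 = 2.25 at q = 10%.

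**Step 7. The paired t test of the 3-to-9-month change.** With a true loss of 2.5 and correlation 0.5, power is 97.2% with LOCF and 97.2% in completers at 10% loss, and 92.6% against 92.7% at 30%. LOCF shrinks the mean and the SD of the change together, so the test hardly moves; the estimate does.

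**The case against.** The strongest case on the other side has five parts.

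1. *At the planned dropout the harm is small.* Even if the whole 10% falls in phase II, the bias is 0.25, one tenth of the difference the plan calls clinically important, and the rejection rate is about 6–7%. This stands. The larger figures need two to three times the planned loss in phase II alone, and the document says only that losses could rise.

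2. *The error rates belong to a test the plan does not single out.* This stands. A reader might infer that the planned interaction test or the paired tests have a false-positive rate of up to 21%. The document does not support that. In the scenario used, the difference between arms changes over time, so the interaction null is false and a rejection there is no error. The paired test still detects the loss almost as often as it does in completers.

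3. *Random dropout alone does not bias LOCF.* Partly right. If the 3-month changes truly persist, LOCF is unbiased on average for phase II losses. A reader might infer that dropout by itself manufactures evidence of maintenance; it does so only when means move after month 3. That possibility is, however, the question phase II is meant to answer.

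4. *LOCF is conservative.* This is true of the 3-month effect when women leave in phase I. It is not true of maintenance, where pulling the change towards zero favours the hoped-for conclusion.

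5. *Missing-data handling belongs in an analysis plan that is not shown.* This would answer a complaint about an unstated sensitivity analysis or covariance structure, and none is made here. It does not answer a method that the article itself selects.

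**Conclusion.** The point holds as a defect in a stated rule and should be fixed. LOCF, three visits and a maintenance objective together mean that each missing 9-month value is filled in as no change since month 3. If means change in phase II, in either direction, the estimated change is (1 − p) times the true one, even with random dropout.

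The size depends on phase II loss, which the document does not give. For a 2.5 benefit fully lost by month 9, the spurious difference is 0.25 at 10% loss, which is modest, and 0.50 to 0.75 at an assumed 20–30%. The corresponding rejection rates of a separate 9-month comparison rest on SD 3.5, 35 per arm, equal random loss in both arms and correlations of 0.3 to 0.7.

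It would go too far to say that LOCF invalidates phase II or hides a lost benefit. At the planned dropout it does neither. The distortion lies mainly in the estimated change and the 9-month difference, and it grows with losses of the kind the article itself foresees.

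**What to change.** Replace LOCF, and the repeated measures ANOVA that needs the filled-in data, with a likelihood-based mixed model for repeated measures on all observed values of all randomised women. Specify two contrasts for phase II: the 3-to-9-month change within each arm and the difference between arms at month 9. Under missing at random, this estimates a true full loss of 2.5 as 2.5, where LOCF would give 2.25, 2.00 or 1.75 at 10%, 20% or 30% loss. No imputation is needed to keep women with incomplete follow-up in the intention-to-treat analysis. The covariance structure and estimation details can be left to the analysis plan.

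Preferably add one multiple-imputation sensitivity analysis in which women lost in phase II return to baseline or are shifted by a stated delta, since leavers may do worse than completers.

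The cost is a documented protocol change with a registry update, because recruitment had begun and the method is published, plus a little programming. The SPSS software named in the plan offers such models (MIXED procedure). Sample size, visits and diets are unchanged.

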### Sample size calculation

Using a type I error of 5% (*α* = 0.05) and a type II error of 20% (*β* = 0.20, power = 80%), and serum HDL-C concentrations as the key variable, the sample size in this study was calculated using the following formula, which has been proposed for parallel clinical trials:$$n=\frac{2\left[{\left({\textrm{Z}}_{1-\frac{\alpha }{2}}+{\textrm{Z}}_{1-\beta}\right)}^2\times {\upsigma}^2\right]}{{\textrm{d}}^2}$$

*n* = sample size for each group.

*σ* = The variance (SD) for mean HDL-C concentrations was as 3.5, which was calculated using the average SDs reported for serum HDL-C in Rajaie et al. study [35].

*d* = The minimal clinically important difference for HDL-C was set at 2.5, based on previous research [38].

Overall, using this formula and assuming a 10% drop-out rate in each group, we will require a sample size of 35 subjects in each group.

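### The sentence on simple two-group comparisons pairs the chi-square test with continuous variables and the t-test with categorical ones, very probably a word-order slip that needs correcting

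*Protocol article*

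**What the plan says.** The Statistical analysis section first sets out how data will be summarised: mean and SD "for continuous variables and as percentages for categorical variables". The next sentence covers comparisons between the two groups. It lists the tests in the order "Chi-square test and independent samples" t-test and states that they "will be used for comparing continuous and categorical variables between the two groups, respectively".

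The section then gives the paired t-test for within-group change. For the treatment question it says: "Repeated measures analysis of variance will be employed to determine the impact of the intervention on the outcome variables", with terms for intervention, time and their interaction.

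The Sample size calculation section takes HDL-C, a continuous variable, as the key variable and applies the usual formula for comparing two means.

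**The concern.** The closing word of the sentence fixes a one-to-one pairing by order. The first test (chi-square) goes with the first variable type (continuous), and the second test (t-test) with the second type (categorical). Both pairings are wrong.

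A Pearson chi-square test on an uncategorised continuous measurement treats each distinct value as an unordered category. It ignores the ordering and spacing of the values, fills the table with tiny expected counts, and does not test a difference in means. In the other direction, the Assessment of variables section collects nominal items such as ethnic origin and marital status. A t-test on these compares averages of arbitrary codes, and the result changes when the categories are renumbered.

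The published protocol is the reference against which the analysis will be judged. As it stands, an analyst who does the sensible thing departs from the stated plan, and one who follows the sentence to the letter produces invalid simple comparisons.

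**Working it through.** **1. The pairing, set out by order**

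| Position | Test named | Variable type named | Conventional test for that type |
|---|---|---|---|
| First | Chi-square | Continuous | Independent-samples t-test |
| Second | Independent-samples t-test | Categorical | Chi-square |

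Both rows are mismatched. Nothing elsewhere in the article restates or corrects the pairing.

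**2. The article's own sample size, which rests on comparing means**

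Inputs from the Sample size calculation section: two-sided alpha ("Using a type I error of 5"%, with the formula using Z at 1 − α/2), power 80%, SD ("for mean HDL-C concentrations was as 3.5"), difference ("The minimal clinically important difference for HDL-C was set at 2.5") and attrition ("assuming a 10% drop-out rate in each group").

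- n = 2 × (1.960 + 0.842)² × 3.5² / 2.5² = 30.77, rounded up to 31 evaluable per group.
- 31 / 0.90 = 34.4, rounded up to 35 per group.

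This reproduces the stated 35. Power for a two-sample comparison of means is about 80% with 31 per group and 85% with 35. The simple two-group test that matches this formula is the t-test, so the sample size section and the literal pairing do not fit together.

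**3. What the literal rule would do to a continuous variable (illustration only)**

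*All values distinct.* With 35 per group there are 70 columns, each holding one observation, and every expected count is 0.5.

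- Each column contributes (1 − 0.5)²/0.5 + (0 − 0.5)²/0.5 = 1.
- Chi-square is therefore always 70 on (2 − 1)(70 − 1) = 69 degrees of freedom, p = 0.44, whatever the true difference. The test can never reject.

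*Values rounded to whole units.* This was simulated with 35 per arm, SD 3.5 and difference 2.5. The mean of 45 in one arm and the whole-unit rounding are assumptions that the article does not give.

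| Recording of HDL-C | Chi-square rejects | t-test rejects |
|---|---|---|
| All values distinct (2,000 runs) | 0% | about 85% |
| Whole units (2,000 and 4,000 runs) | about 16% | about 84–85% |

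**4. Which analyses the sentence governs**

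- Simple comparisons of two groups, at baseline or unadjusted: governed by the sentence and affected.
- Within-group change: assigned to the paired t-test, not affected.
- Effect of the intervention on outcomes: assigned to repeated measures ANOVA, not affected.
- Sample size: with the pairing put right it remains 31 evaluable and 35 enrolled per group.

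**The case against.** The strongest reply is that this is a slip of word order that no competent analyst would follow. The preceding sentence attaches mean and SD to continuous variables and percentages to categorical ones. The same section plans a Kolmogorov-Smirnov test, histograms, Q-Q plots and log transformation to reach normality, which would serve little purpose if continuous data went to chi-square. The trial is also sized on two means. All of this stands, and it makes the intended meaning fairly clear. It does not make the sentence correct: the rule sits in the operative analysis text, is complete, and is wrong as stated.

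A second reply concerns reach, and it also stands. A reader might infer that the trial's treatment comparisons as a whole are invalid, or that HDL-C, glucose and bacterial load will be tested for a diet effect by chi-square. The article does not support that. The sentence names no variable, and the intervention effect has its own named method, whose validity does not depend on this sentence.

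A third reply is that the simulated figures do not describe a realistic risk. That is fair. Cross-tabulating every distinct HDL-C value is implausible given the planned normality checks, and the 16% depends on the assumed rounding. The figures show why the literal rule is untenable; they do not forecast a loss of power in this trial.

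**Conclusion.** The point holds as a wording error of limited reach. Read literally, the sentence reverses the tests for the simple two-group comparisons, and following it would make those comparisons invalid. It is very probably unintended.

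No stated figure changes. The sample size is reproduced at 35 per group, and the ANOVA and paired t-tests are untouched. The drop from about 84–85% to 16% or 0% should not be read as lost power for the trial's key variable. It rests on an assumed mean of 45 in one arm, on the recording precision, and on a literal execution that the rest of the section makes unlikely.

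The conclusion itself needs no numerical assumption. It follows from the order of the words and from the absence of any correcting statement in the article.

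**What to change.** Swap the two test names and leave the rest of the sentence alone: the independent-samples t-test and the chi-square test, in that order, "will be used for comparing continuous and categorical variables between the two groups, respectively". Naming Fisher's exact test for small expected counts would be a reasonable optional addition, but it is not needed to cure the error.

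The cost is one sentence of wording, with no change to design, data collection, sample size or the main analysis. The article already says that protocol modifications will be communicated and the registry updated, so the correction can go by that route.

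### The repeated-measures ANOVA leaves the role of baseline open, and on either reading its stated terms do not isolate the 3-month diet effect; on one reading they do not answer the maintenance aim either

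*Protocol article*

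**What the plan says.** The Statistical analysis section of the protocol article assigns the impact of the intervention to a repeated-measures ANOVA and names its terms: "These analyses will examine the effects of the intervention, time, and the interaction between time and intervention". It adds that any baseline differences in the outcomes, along with diet and physical activity, will be controlled in these analyses. It does not say whether baseline is also one of the time levels, and it names no arm comparison at a given visit.

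The same section lists a paired "test for within-group comparisons". It also says that the chi-square test and the independent-samples t-test, in that order, "will be used for comparing continuous and categorical variables between the two groups, respectively".

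Biochemical assessments gives three blood samples: baseline, 3 months and 9 months. The aims at the end of Background pose two questions: the effect of the diet, and whether changes in the gut microbiota "will be sustained during a subsequent six-month weight maintenance phase". Intervention repeats the second question and puts both arms on the same maintenance diet for those six months.

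Sample size calculation uses one comparison of two means: "The minimal clinically important difference for HDL-C was set at 2.5", with an SD "for mean HDL-C concentrations was as 3.5". It names no visit.

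**The concern.** The trial asks two different things of three measurements. The diet effect is the arm difference at the end of the 3-month diet phase. Maintenance concerns what becomes of that difference by 9 months. A main effect of intervention pools over visits. A three-level interaction asks only whether the two arms' profiles differ in any way.

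If baseline is a time level, the main effect includes a visit at which randomisation makes the expected difference zero. The interaction then cannot tell a lasting benefit from one that has vanished. Several terms would be available, none named as the one that answers each aim, and the choice could be made after the data are seen.

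Within-arm paired tests do not fill the gap. Both arms are energy-restricted and all women are selected on abnormal metabolic values, so change is expected in both arms whatever the carbohydrate content. Separately, the sentence on between-group tests gives each test the wrong type of variable.

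**Working it through.** **Inputs from the article.** Difference 2.5, SD 3.5, two-sided alpha 0.05, power 80%, 10% drop-out, 35 per arm (Sample size calculation); visits at 0, 3 and 9 months (Biochemical assessments).

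**Assumptions not in the article.** The 2.5 difference applies at 3 months. The SD is the same at every visit. All pairs of visits have the same correlation ρ, shown at 0.3, 0.5 and 0.7. The 9-month difference is 2.5 (kept) or 0 (lost).

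**1. The plan's own figure.** n = 2(1.96 + 0.84)² × 3.5² / 2.5² = 30.77 (unrounded normal quantiles), so 31 per arm. 31 / 0.9 = 34.4, so 35. The stated sample size reproduces. The checks below use n = 31 per arm.

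**2. Baseline as a time level: main effect.**
- Estimate = (0 + 2.5 + d9) / 3, which is 5.0/3 = 1.67 if kept and 2.5/3 = 0.83 if lost.
- SE = 3.5 × √((1 + 2ρ)/3) × √(2/31). At ρ = 0.5 this is 0.726.
- Power is from the noncentral t with 60 df.

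**3. Baseline as a time level: interaction.**
- Noncentral F with 2 and 120 df, λ = (31/2) × Σ(d − mean d)² / (3.5²(1 − ρ)).
- Kept: d = (0, 2.5, 2.5), Σ = 2.78 + 0.69 + 0.69 = 4.17.
- Lost: d = (0, 2.5, 0), Σ = 0.69 + 2.78 + 0.69 = 4.17.
- The two sums are equal, so λ is equal (10.54 at ρ = 0.5). Power is therefore identical for any correlation.

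**4. Levels 3 and 9 months only, baseline as covariate.**
- Main effect = (2.5 + d9)/2, which is 2.5 if kept and 1.25 if lost. Its SE at ρ = 0.5 is 3.5 × √((1 + ρ)/2 − ρ²) × √(2/31) = 0.629, which gives 50% power if lost.
- Interaction = change in the arm difference, SE = 3.5 × √(2(1 − ρ)) × √(2/31), which is 0.889 at ρ = 0.5.

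**5. Baseline-adjusted contrast at 3 months.** SE = 3.5 × √(1 − ρ²) × √(2/31), which is 0.770 at ρ = 0.5. It does not depend on what happens at 9 months.

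| Test | ρ = 0.3 | ρ = 0.5 | ρ = 0.7 |
|---|---|---|---|
| Main effect, baseline a level, kept / lost | 71% / 24% | 62% / 20% | 54% / 18% |
| 2-df interaction, baseline a level, kept / lost | 68% / 68% | 83% / 83% | 97% / 97% |
| 1-df interaction, 3 and 9 months only, kept / lost | 5% / 65% | 5% / 79% | 5% / 95% |
| Adjusted 3-month contrast | 83% | 89% | 97% |

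At ρ = 0.5 the matching adjusted 9-month contrast has 89% power if the effect is kept and rejects at the 5% level if it is lost, so it separates the two cases. Simulation with 6,000 trials per setting agreed with the figures for the main effect, the 2-df interaction and the adjusted contrasts to within about one percentage point.

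**6. Paired tests.** Suppose both arms truly change by the same 1.25 at ρ = 0.5. Each paired test then has power 0.486, so exactly one arm is significant with probability 2 × 0.486 × 0.514 = 50%. A significant change in one arm only is thus no evidence of a diet effect.

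**The case against.** The strongest reply is that the article never calls baseline a time level. Its statement that baseline differences will be controlled fits a model of the 3- and 9-month values with baseline as covariate, which is close to the model recommended here. On that reading the interaction is a direct test of whether the arm difference changes, with 65% to 95% power against complete loss. This stands, and it is why the figures in steps 2 and 3 are conditional. It does not rescue the main effect, which then averages two visits.

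A reader might infer that the planned analysis answers neither aim. That is too strong. Even with baseline as a level, the interaction is a valid randomised comparison of the arms' profiles, and at ρ = 0.7 it has the same 97% power as the recommended contrast. The article also does not make the main effect its decision term.

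A reader might also infer that no planned test compares the arms at 3 months, although the sample size rests on that comparison. The sample size section names no visit, and an independent-samples t-test between arms is listed, also without a visit. The comparison is unspecified rather than excluded.

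Nor does the article say that paired tests will be used to claim a diet effect, that maintenance will be concluded from a non-significant change, or that baseline is adjusted for only when it differs.

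Finally, visit-specific contrasts are often left to an analysis plan, and none is shown. That is a fair limit. The point here rests on the terms that the article does fix and on its two unreconciled indications about baseline.

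**Conclusion.** The point holds in a limited form. The role of baseline is ambiguous, and on neither reading is the intervention main effect the 3-month arm difference. If baseline is a time level, the main effect shrinks 2.5 to 1.67 or 0.83, and the interaction cannot distinguish full maintenance from full loss. If only 3 and 9 months are levels, the maintenance aim does have a test. The power figures rest on the assumed correlations, equal SDs and placing the 2.5 difference at 3 months. The equality of interaction power in the kept and lost cases holds for any common correlation. The reversed pairing of tests and variable types is a plain error that needs no assumption. The sample size of 35 per arm is not in question. This should be corrected: it removes an ambiguity at no cost, but it does not show that the planned tests are invalid.

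**What to change.** 1. Model the 3- and 9-month values as outcomes, with arm, visit, arm-by-visit and the baseline value of the outcome always included as a covariate. State that baseline is not a time level.
2. Name three estimates, each with a 95% CI: the arm difference at 3 months (the diet effect), the arm difference at 9 months, and the 3-to-9-month change in that difference (maintenance).
3. Label the within-arm paired t-tests descriptive.
4. Correct the sentence on between-group tests: t-test for continuous variables, chi-square test for categorical variables.

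The cost is wording in the analysis section or analysis plan. Visits, data, sample size and software are unchanged.
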